### Data collection

This study will employ both self-reported and objective measures to comprehensively assess participants’ PL, engagement in physical activities, and sports video gaming habits.

Self-reported data will be collected through a structured set of online questionnaires (see Appendix 1), which include items on video gaming behavior, physical activity levels, physical literacy, and demographic information. These questionnaires will be administered by trained research assistants using Qualtrics, a secure and institution-approved online survey platform. Access to the survey will be provided via a secure link or QR code, distributed to students by their teachers.

Objective measures will include assessments of simple reaction time and eye-hand coordination, conducted using the Ruler Drop Test (RDT) and the Alternate Hand Wall Toss Test (AHWT), respectively. Additionally, a knowledge-based quiz will be administered to evaluate participants’ cognitive understanding of tennis (see Appendix 2).

All assessments will be conducted during scheduled PE tennis lessons at the CUHK. Data collection will occur at three time points: baseline, post-intervention, and a three-week follow-up. Baseline data collection is scheduled for the first week of the second semester (early January 2026), during the same lesson in which participants are recruited. This will be followed by a six-week sports video gaming (SVG) intervention. Post-intervention assessments will be conducted in Week 8 (early March 2026), and a three-week follow-up assessment will take place in Week 11 (late March 2026).

The participant timeline is illustrated in Fig 1. To ensure consistency across all groups, identical procedures and instruments will be used. All assessments will be administered by the principal researcher in collaboration with trained research assistants. A summary of the measurement tools and outcome variables is provided in Table 1.

**Table 1 pone.0343594.t001:** Summary of measurements in this study.

Instrument/Method used	Outcome assessed	Type	Physical literacy domain	Reference
Custom questionnaire on video gaming	Video gaming habits and demographics	Self-reported	Not applicable	Developed by researcher
International Physical Activity Questionnaire – Short Form (IPAQ-SF)	Physical activity level	Self-reported	Physical	[22]
Perceived Physical Literacy Instrument (PPLI)	Perceived physical literacy	Self-reported	Affective, social, cognitive	[23]
Sport Motivation Scale-6 (SMS-6)	Motivation for sport participation	Self-reported	Affective	[25]
Selected items from Adolescent Physical Literacy Questionnaire (APLQ)	Social engagement in physical activity	Self-reported	Social	[24]
Ruler Drop Test (RDT)	Simple reaction time	Objective	Physical	[26]
Alternate Hand Wall Toss Test (AHWT)	Eye-hand coordination	Objective	Physical	[27]
Researcher-designed multiple-choice quiz	Knowledge of tennis	Objective	Cognitive	Developed by researcher

**Fig 1 pone.0343594.g001:**
[figure not shown]
Participant timeline schematic diagram. Week 1 included briefing, enrollment, and baseline assessment. Weeks 2-7 comprised the 6-week SVG intervention. Post-intervention assessment was conducted in Week 8, followed by a 3-week follow-up assessment in Week 11.

1. **Demographic information**

Participants will provide demographic details including age, gender, ethnicity, academic department and faculty, sports regularly participated in, and years of involvement in those sports. The details will be collected in the beginning of the online questionnaire.

2. **Self-reported measures**

To capture participants’ behaviors and perceptions across relevant domains, a series of self-reported instruments will be administered via an online questionnaire.

i) *Video gaming habit*

Participants will respond to questions regarding their video gaming behaviors, including frequency, duration, devices used, and types of games played. Sample items include:

“How much time per week you play video games?”“How many days per week do you play video games?”“How long have you been playing video games?”

Participants who indicate regular gaming activity will be asked additional questions specific to sports video gaming (SVG), such as:

“Which types of sports video games you play?”“How much time per week you play sports video games?”“How many days per week do you play sports video games?”

ii) *Physical activity level*

Participants’ physical activity levels will be assessed using the International Physical Activity Questionnaire – Short Form (IPAQ-SF)**.** This instrument evaluates the frequency and duration of physical activities across different intensities: vigorous, moderate, and walking, as well as time spent sitting, over the past seven days. It provides an estimate of total physical activity expressed in MET-minutes per week. A sample item includes:

“During the last 7 days, on how many days did you do vigorous physical activities like heavy lifting, digging, aerobics, or fast bicycling?”

The IPAQ-SF is suitable for use with individuals aged 15 years and older. Its reliability and validity have been supported by a large-scale international study conducted by Craig et al. [22], which involved participants from 12 countries. The study reported acceptable test-retest reliability, with correlations typically exceeding 0.80, and moderate criterion validity, with correlations ranging from 0.30 to 0.50 when compared to accelerometer data.

iii) *Perceived physical literacy*

To assess PL comprehensively, we adopted a multi-instrument approach. Perceived PL will be measured using the Perceived Physical Literacy Instrument (PPLI), a 9-item scale comprising three subscales: *knowledge and understanding*, *self-expression and communication with others*, and *sense of self and self-confidence*. Responses are recorded on a 5-point Likert scale. The instrument has demonstrated satisfactory construct validity (RMSEA = 0.08; CFI = 0.94; SRMR = 0.04) and convergent validity (CR = 0.72–0.78; AVE = 0.43–0.54) in adolescent populations [23].

iv) *Social engagement in physical activities*

To assess the social dimension of PL, four items from the Adolescent Physical Literacy Questionnaire (APLQ) will be employed. The APLQ is a validated 25-item instrument designed to measure various domains of physical literacy among adolescents [24]. It was selected because it is the only available validated tool that explicitly includes the social domain, which was central to this study’s objectives. For the purposes of this study, four items specifically targeting social engagement in physical activities have been selected. Participants will respond to each item using a 5-point Likert scale ranging from “strongly disagree” to “strongly agree.”

The selected items are:

“I do sports and physical activity with family or friends.”“I encourage others to do sports and physical activity with me.”“I participate in group sports outside of school time.”“I have made new friendships in sport and physical activity.”

These items are intended to capture participants’ interpersonal experiences and social involvement in physical activity, which are recognized as key components of PL development.

v) *Motivation in engagement in sports*

Motivation for engaging in sports will be assessed using the Sport Motivation Scale-6 (SMS-6), a 24-item instrument designed to measure contextual motivation in sport. The scale includes six subscales representing different types of intrinsic and extrinsic motivation. Responses are recorded on a 7-point Likert scale. The SMS-6 has demonstrated satisfactory construct validity in athletic populations [25].

3. **Objective measures**

To complement the self-reported data, three objective assessments will be conducted to evaluate participants’ physical and cognitive performance: simple reaction time, eye-hand coordination, and cognitive knowledge in tennis.

i) *Simple reaction time*

Simple reaction time will be measured using the Ruler Drop Test (RDT). A 50-cm ruler will be used for the assessment. Participants will be seated with their arm in a mid-prone position and elbow flexed at 90°. The ruler will be held vertically with the zero-mark aligned at the participant’s fingertips. Upon release, participants will attempt to catch the ruler as quickly as possible. The distance the ruler falls before being caught will be recorded in centimeters. Each participant will complete three trials with each hand, and the average of the three measurements will be used for analysis. Prior to testing, participants will be given several practices attempts to familiarize themselves with the procedure. Reaction time will be calculated based on the distance fallen, using the standard formula for free fall under gravity [26].

ii) *Eye-hand coordination*

Eye-hand coordination will be assessed using the Alternate Hand Wall Toss Test (AHWT), a widely used measure in sports medicine [27]. Participants will stand 2.0 meters from a wall and throw a tennis ball underhand with one hand, attempting to catch it with the opposite hand. The sequence will alternate between right-hand throws with left-hand catches and vice versa. The total number of successful catches within 30 seconds will be recorded. Each participant will complete two trials, and the best score will be used for analysis. Practice attempts will be allowed before the formal assessment.

iii) *Cognitive knowledge in tennis*

Cognitive understanding of tennis will be evaluated using a researcher-designed multiple-choice quiz consisting of ten items, each with four answer options (see Appendix 2). The quiz covers essential content areas including tennis rules, terminology, court layout, tactics, and skill-related knowledge. Items were developed collaboratively by PE teachers with expertise in tennis, drawing from both the instructional content of the tennis PE course and the tennis-related elements embedded in the SVG.

The quiz was pilot-tested with a small group of university students (*n* = 10) to evaluate clarity and appropriateness for the target population. Feedback from the pilot group informed refinements to the questions, supporting the content validity of the instrument. Although the quiz has not undergone formal psychometric validation, it is tailored to reflect the specific learning objectives of the intervention. To minimize response bias, the order of answer choices will be randomized across different assessment time points. Sample questions include:

“What is the term for a serve that the opponent cannot touch?”“What happens if a player serves two consecutive faults?”“Which strategy involves hitting the ball deep into the opponent’s court to push them back?”“What is the primary goal of the “one up, one back” formation in doubles?”

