*Physical Competence***:** Participants in the intervention group will demonstrate greater improvement in perceptual-motor skills, specifically simple reaction time and eye-hand coordination, compared to those in the control group. These measures represent targeted components within the physical domain of PL and align with the perceptual-motor demands of both sports video gameplay and real-life tennis, rather than comprehensive motor competence.*Motivation for real-life sports***:** Participants in the intervention group will report a greater increase in motivation to engage in real-life sports compared to those in the control group.*Cognitive knowledge of tennis:* Participants in the intervention group will achieve a greater improvement in cognitive knowledge related to tennis than participants in the control group.*Social engagement in physical activities*: Participants in the intervention group will exhibit greater enhancement in in-person social interaction relative to the control group.*Physical activity engagement:* Participants in the intervention group will show a higher increase in physical activity engagement levels than their counterparts in the control group.

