The first two sessions will include guided tutorials within the game to help participants become familiar with the controller layout and basic tennis concepts. For example, the initial tutorial focuses on repositioning, requiring players to return to the center area behind the baseline after each shot. An instructional video will explain the importance of repositioning and demonstrate how to control the avatar. Participants must successfully complete six repositioning tasks to move forward. From the third session onward, participants will engage in both singles and doubles matches, playing with or against other participants. No gaming sessions will be provided to the control group. Participants may withdraw from the intervention if they experience scheduling conflicts, physical discomfort, musculoskeletal or cardiovascular conditions, or are unable to comply with the intervention protocol. To support adherence, PE teachers and research assistants will regularly remind participants to attend their gaming sessions. Additionally, all participants in the intervention and control groups will receive four participation marks in their PE course upon completing the study.

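### The social-engagement items, as printed, do not separate real-life sport from the trial's own gaming sessions; the risk lies mainly in the cumulative friendship item

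*Protocol article*

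**What the plan says.** The Introduction of the Protocol article states hypothesis 4 under a heading on social engagement in physical activities, but words it more broadly: "Participants in the intervention group will exhibit greater enhancement in in-person social interaction relative to the control group".

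The outcome is described under Data collection, self-reported measures, iv) Social engagement in physical activities. Four of the 25 APLQ items are used, each on a 5-point agreement scale:

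1. "I do sports and physical activity with family or friends"
2. "I encourage others to do sports and physical activity with me"
3. "I participate in group sports outside of school time"
4. "I have made new friendships in sport and physical activity"

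The same section says the items are meant to capture "interpersonal experiences and social involvement in physical activity". The article text gives them no time window and no instruction about the gaming sessions. The full questionnaire is in Appendix 1, which is not shown. By contrast, the IPAQ-SF in the same questionnaire covers the past seven days.

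Under Intervention, the first two sessions are tutorials; from the third, "participants will engage in both singles and doubles matches, playing with or against other participants". Controls receive no sessions. That section also presents multiplayer play as serving the social side of physical literacy. Sessions run in Weeks 2 to 7, with assessments in Weeks 8 and 11.

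**The concern.** The trial gives one arm a new, scheduled place to meet other students and then asks both arms whether they have made friends in sport. The sessions are labelled sports video gaming. An intervention student who got to know someone at the SVG Corner could reasonably agree more strongly with item 4, although nothing in that student's real-life sport has changed. No comparable route exists in the control arm, so any such effect favours hypothesis 4.

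The Introduction says the intervention aims at motivation for real-life tennis and not at more video gaming. If session contact feeds the score, part of a reported gain in social engagement in physical activity would be contact within the intervention itself.

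Item 4 also complicates follow-up. A friendship made in Week 4 is still a true answer in Week 11, so for that item persistence after the sessions cannot be told apart from a carried-over answer.

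**Working it through.** The plan gives no figure on this point, so there is none to reproduce. The check has two parts.

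**Reading the items**

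| Item | Tense | Could seated gaming count on the wording? | Could the answer fall by Week 11? |
|---|---|---|---|
| 1 | present | only if the student regards the game as sport | yes |
| 2 | present | poor fit | yes |
| 3 | present, outside school time | very poor fit: the SVG Corner runs on weekdays, 10:00–13:00 and 14:00–18:00 | yes |
| 4 | present perfect | yes, for friendships made at the sessions | unlikely |

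The exposure is greatest for item 4, with item 1 a distant second. Item 4 is one of four items, or 25% of the score.

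**Size (illustration)**

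Inputs from the article: 88 students per arm (Study design); design effect 1.42, from 22 per class and ICC 0.02 (Sample size calculation); significance level 0.05, taken as two-sided (Data analysis). Assumptions, because the article gives no values: SD of the four-item mean 0.8 (range 0.6 to 1.0), and 10% to 30% of intervention students moving one step on the affected items because of session contact.

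Shift in the four-item mean = share × items affected × 1 step / 4.

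- Item 4 only: 0.10 × 1 / 4 = 0.025; 0.30 × 1 / 4 = 0.075 points. Divided by 0.8: 0.03 to 0.09 SD.
- Items 1 and 4: 0.10 × 2 / 4 = 0.05; 0.30 × 2 / 4 = 0.15 points. Divided by 0.8: 0.06 to 0.19 SD.

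Smallest significant arm difference at one visit = critical value × SD × √(2 × 1.42 / 88).

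- √(2.84 / 88) = 0.180.
- Normal critical value, SD 0.8: 1.96 × 0.8 × 0.180 = 0.28 points. For SD 0.6 to 1.0: 0.21 to 0.35.
- t with 6 df (8 classes), SD 0.8: 2.447 × 0.8 × 0.180 = 0.35 points. For SD 0.6 to 1.0: 0.26 to 0.44.

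At SD 0.8, against the threshold of 0.28, the item-4-only shift is 0.025 / 0.28 = 9% to 0.075 / 0.28 = 27%. The two-item shift is 0.05 / 0.28 = 18% to 0.15 / 0.28 = 54%, about half at most. For item 4 alone to produce significance, the arm difference on that item would have to be four times the threshold: 0.85 to 1.41 points (normal) or 1.05 to 1.76 points (t) on a 5-point scale, over the SD range.

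This threshold is for a single-visit comparison. The planned mixed model also uses the baseline score, which could move the threshold either way, depending on the correlation between visits; the article does not give that correlation.

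**What dropping item 4 would achieve**

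If only item 4 is affected, the three-item mean shifts by 0. If item 1 is affected as well, it shifts by 0.10 / 3 = 0.03 to 0.30 / 3 = 0.10 points. The three-item score therefore removes the main route but not all of it; the instruction line addresses the rest.

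**The case against.** Much of the case on the other side stands.

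- Appendix 1 may already contain an instruction line. Its absence is established only for the article text.
- Items 1 to 3 ask about sport, group sport or physical activity. The article describes the game as seated and sedentary and contrasts it with real-life sport, and the questionnaire asks about video gaming separately. Read literally, these items do not count gaming.
- Match play starts at the third session. At two sessions a week, that leaves about five weeks of it, not six.
- Social engagement is a secondary outcome under Data analysis, and the Limitations call the social measure exploratory and advise caution.
- Peer contact through multiplayer play is an intended mechanism, and hypothesis 4 speaks of in-person interaction. Whether friendships made at the sessions should count is partly a choice of construct.

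A reader might infer that hypothesis 4 can be met simply by playing in the SVG Corner, or that the Week 11 score cannot show whether an effect lasted. The documents support neither. The first would need contamination across several items, or a very large shift in item 4. The second is a problem for item 4 only; items 1 to 3 can fall after the sessions end.

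The objections do not remove the narrower point. The caveats in the Limitations concern missing validated tools and general self-report bias, not a source of answers present in one arm only. The construct argument does not settle it either, because both the heading of hypothesis 4 and the stated purpose of the items refer to physical activity.

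**Conclusion.** The point holds in a limited form. As printed, the items do not separate real-life sport from the gaming sessions. Item 4 can rise in the intervention arm alone and is unlikely to fall back by Week 11; items 1 to 3 are much less exposed. The social score may be modestly biased towards hypothesis 4, and its Week 11 value is blurred but still informative.

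Under the assumed shares and SD 0.8, the bias is 0.03 to 0.09 SD through item 4 alone and at most 0.19 SD if item 1 is affected too. That would not by itself reach significance, but it could add to a real or chance difference in the hypothesised direction. The shares and the SD are assumptions, and the conclusion also depends on Appendix 1 not already holding the instruction.

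**What to change.** First check Appendix 1. If it has no such instruction, add one line above the four items, identical in both arms and at all three visits, for example: *Please answer about real-life sport and physical activity; do not count video gaming.* Leave the item wording unchanged.

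Report item 4 separately by arm and visit, and prespecify a sensitivity analysis of the three-item score without it. If baseline data have already been collected, keep the questionnaire as it is, so that visits stay comparable; the separate report and the three-item analysis remain possible.

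A three-week recall window is less attractive. At Week 8 it would omit friendships made in the early intervention weeks. At Week 11 it would make item 4 a question about newly formed friendships and not about lasting ones. It would also alter the published items.

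The cost is one line in the online questionnaire, a minor departure from the published administration of the items, and one extra analysis.

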### Ethics approval and consent to participate

Ethical approval for this study has been obtained from the Survey and Behavioural Research Ethics Committee of CUHK (Ref. No.: SBRE-24–0047). All procedures involving human participants will be conducted in accordance with the ethical standards of the institutional and/or nation research committee and with the 2024 revision of the Declaration of Helsinki (https://www.wma.net/policies-post/wma-declaration-of-helsinki/). Written informed consent will be obtained from all participants prior to their involvement in the study.

### Dissemination plan

Findings from the study will be disseminated through peer-reviewed journal publications, presentations at international conferences, and academic lectures. For requests related to secondary data analysis, interested parties should contact the corresponding author for permission.

### Data analysis

Descriptive statistics, including means and standard deviations, will be calculated for university students’ video gaming time, gaming frequency, physical activity levels, physical literacy, reaction time, and eye-hand coordination across all relevant subscales and instruments. To examine baseline differences between groups in the cross-sectional study, one-way analyses of variance (ANOVAs) will be conducted.

To evaluate intervention effects, mixed-effects models will be employed instead of simple repeated-measures ANOVAs to account for the hierarchical structure of the data and potential intra-cluster correlation among participants within the same class group. This approach addresses the reality that, although courses follow standardized content, variability in teaching style, instructor enthusiasm, and informal reinforcement of the intervention is inevitable in real-world PE settings. Mixed-effects models will include fixed effects for time (baseline, post-intervention, follow-up) and group (intervention vs. control), as well as random effects for class clusters to capture variability across different teaching contexts. These models will assess both main effects and interaction effects, providing more accurate standard error estimation and valid statistical inference.

For secondary outcomes (motivation, cognitive knowledge, social engagement, and physical activity), similar mixed-effects or generalized estimating equation models will be applied, depending on distributional assumptions. Multiple linear regression analyses will explore predictive relationships between PL and physical activity levels, with SVG gaming included as a potential mediator or moderator. Covariates such as baseline physical activity, prior SVG experience, and demographic characteristics (age, gender) will be adjusted for in all models. Interaction effects between the intervention and participant characteristics (e.g., gender, gaming experience) will also be examined to identify subgroup differences.

To enhance the interpretability and transparency of our findings, partial eta-squared will be reported for all primary outcomes to indicate the magnitude of observed effects. Additionally, 95% confidence intervals will be provided to reflect the precision of the estimates and the range within which the true effect is likely to fall. These metrics will support a more nuanced understanding of the intervention’s impact and facilitate comparison with other studies.

To ensure the integrity of the analysis, the following procedures will be used to address missing data. Participants with more than 20% missing responses on key outcome measures (e.g., physical literacy or physical activity questionnaires) may be excluded from specific analyses. All decisions regarding missing data handling will be documented in the final report, including the rationale for exclusion or imputation. All statistical analyses will be performed using SPSS Version 30 for Windows, with the significance level set at *p* < 0.05.

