### Participants

#### Sample size calculation.

Given that the hypotheses in this study involve both between-subjects comparisons (intervention vs. control groups) and within-subjects measurements across three time points, the sample size was calculated using the *“ANOVA: Repeated measures, within-between interaction”* option in G*Power 3.1 software. Based on an expected medium effect size (f = 0.25), an alpha level of 0.05, and a desired statistical power of 0.80, the required sample size was determined to be 28 participants per group. The choice of f = 0.25 was informed by Cohen’s conventional benchmarks and supported by findings from related educational and exergaming interventions. For instance, Zhao et al. [21] conducted a meta-analysis of 16 randomized controlled trials involving 2,962 students and found that exergames significantly improved PE learning outcomes, with a standardized mean difference (SMD) of 0.45, which corresponds to a medium effect size. Given the educational nature of our intervention and the exploratory context, this estimate was considered both conservative and realistic. To account for an anticipated dropout rate of 20%, the target sample size was increased to 35 participants per group, resulting in a minimum total of 70 participants. To ensure sufficient power and account for unforeseen attrition, more participants than the minimum required will be recruited.

Since this study employs a cluster randomized controlled trial design, it is essential to account for the intra-cluster correlation (ICC) to avoid underestimating the required sample size. Participants within the same class may exhibit correlated outcomes due to shared learning environments and peer interactions. To adjust for clustering, we applied the design effect formula:

Design Effect=1+(m−1)×ICC

Where:

*m* = average cluster size (22 students per class)*ICC* = assumed intra-cluster correlation (conservatively estimated at **0.02** based on similar educational interventions)

Thus:

Design Effect=1+(22−1)×0.02=1+21×0.02=1.42

The adjusted sample size becomes:

70×1.42≈100 participants

To ensure adequate power and account for potential attrition and clustering effects, we plan to recruit 176 participants across 8 classes, which exceeds the adjusted minimum requirement.

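### The intervention model names a random effect for class but no within-participant term and no class-by-time term, so, fitted as listed, it misstates the standard error of the group-by-time effect

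*Protocol article*

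**What the plan says.** All references are to the protocol article. Study design sets three assessments per student in eight classes of 22, four classes per arm. Sample size calculation describes the hypotheses as involving "within-subjects measurements across three time points" as well as the comparison between arms.

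Data analysis replaces repeated-measures ANOVA with mixed-effects models. These have fixed effects for time and group, "as well as random effects for class clusters to capture variability across different teaching contexts". The correlation named as the reason is "potential intra-cluster correlation among participants within the same class group". The section says teachers will inevitably differ in how they teach and in how far they back the intervention informally. It then claims: "These models will assess both main effects and interaction effects, providing more accurate standard error estimation and valid statistical inference". For secondary outcomes, "similar mixed-effects or generalized estimating equation models will be applied, depending on distributional assumptions".

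No participant random effect, within-participant covariance or class-by-time effect is named.

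**The concern.** The hypotheses in the Introduction concern greater improvement in the intervention group, so the test that matters is group-by-time. Two things go wrong with its standard error if the listed terms are the whole model.

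- **No participant term.** A student's three scores are treated as independent given class. Stable differences between students remain in the residual, although they cancel from each student's own change. The standard error is too large.
- **No class-by-time term.** A class intercept shared by all visits cancels from the change contrast. Baseline is in Week 1 and the intervention runs in Weeks 2 to 7, so teacher differences that act during the intervention appear as class-specific change. The listed class effect cannot carry the variability that the section gives as its reason. The standard error is too small.

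The errors pull in opposite directions and offset each other only by chance. At stake are the p-values and 95% confidence intervals of the intervention tests, and the power to detect a real effect.

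**Working it through.** **The plan's own figures.** 28 per group with 20% dropout: 28/0.8 = 35, so 70 in total. Design effect 1 + 21 × 0.02 = 1.42. 70 × 1.42 = 99.4, or about 100. This arithmetic reproduces. It supplies the ICC of 0.02 used below. The protocol gives no standard error for the group-by-time effect.

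**Inputs from the protocol.** 4 classes × 22 = 88 students per arm; ICC 0.02; two-sided alpha 0.05; a standardised difference of 0.45, cited in Sample size calculation.

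**Assumptions, because the protocol gives no figure.** Total variance is 1. The correlation ρ between two visits of one student is 0.3 to 0.8. The class variance is fully, half or not stable over time. There are no dropouts.

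**Variance parts.** C = stable class variance; T = class-by-time variance, with C + T = ICC; P = participant variance = ρ − C; R = residual = 1 − ρ − T.

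**Variance of the difference between arms in post-minus-baseline change:**

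- Correct: 2 × (2T/4 + 2R/88) = T + R/22
- As implied by the class-only model: 2 × 2(T + P + R)/88 = (T + P + R)/22
- As implied with a participant effect added but no class-by-time effect: (T + R)/22

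Type I error is 2 × P(Z > 1.96 × model SE / correct SE).

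**Example: ICC 0.02, class effects stable, ρ = 0.5.** T = 0, P = 0.48, R = 0.50. Correct SE = √(0.50/22) = 0.151. Class-only SE = √(0.98/22) = 0.211. The ratio is 1.40 and type I error is 0.6%.

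**Results at ICC 0.02:**

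| Class effect over time | ρ | Correct SE | Class-only SE | Type I, class only | Type I, participant effect added, no class-by-time |
|---|---|---|---|---|---|
| Stable (T = 0) | 0.3 | 0.178 | 0.211 | 2.0% | 5% |
| | 0.5 | 0.151 | 0.211 | 0.6% | 5% |
| | 0.8 | 0.095 | 0.211 | <0.1% | 5% |
| Half stable (T = 0.01) | 0.3 | 0.203 | 0.212 | 4.1% | 9% |
| | 0.5 | 0.180 | 0.212 | 2.1% | 10% |
| | 0.8 | 0.137 | 0.212 | 0.2% | 17% |
| Not stable (T = 0.02) | 0.3 | 0.226 | 0.213 | 6.4% | 12% |
| | 0.5 | 0.204 | 0.213 | 4.1% | 15% |
| | 0.8 | 0.168 | 0.213 | 1.3% | 27% |

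**Larger class-by-time variance (class-only model, C = 0).** At T = 0.05 the correct SE is 0.282 to 0.238 for ρ = 0.3 to 0.8, against 0.213 from the model; type I error is 14% to 8%. At T = 0.10 the correct SE is 0.357 to 0.323 and type I error is 24% to 20%.

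**Simulation check.** The class-only model was fitted by REML in 300 runs at ICC 0.02 with stable class effects and ρ = 0.5 among students of one class. The mean model SE was 0.2095, the empirical SD 0.1485 and type I error 0.3%. The correct formula gives √(0.49/22) = 0.149 for that case.

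**Power for a 0.45 SD difference, ICC 0.02, ρ = 0.5.** The class-level analysis has 8 − 2 = 6 df, critical t = 2.447 and noncentrality 0.45/SE.

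| Class effect over time | Noncentrality | Power, t on 6 df | Power, class-only model |
|---|---|---|---|
| Stable | 0.45/0.151 = 2.98 | 70% | about 60% |
| Half stable | 0.45/0.180 = 2.50 | 56% | 58% |
| Not stable | 0.45/0.204 = 2.20 | 46% | 56% |

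**The case against.** **The list may not be complete.** The section says what the models will include, not that nothing else will be in them. The plural for class random effects could cover a class-level time slope, SPSS allows a repeated-measures residual covariance, and a condensed article may leave such detail to an analysis plan that is not shown. This stands as a limit: the standard error is wrong if the listed terms are the model. It does not remove the point. The section specifies a model, describes clustering only as students within classes and asserts valid inference; an analyst who follows it would fit the faulty model.

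**A reader might infer a false-positive rate of 10% to 25%.** The documents do not support that for the listed model. It needs class-by-time variance of 0.05 to 0.10, which is 2.5 to 5 times the protocol's whole ICC. At ICC 0.02 the class-only model is mainly conservative.

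**A reader might infer that the repair lifts power from about 60% to about 85%.** The 85% assumes no class-by-time variance and a normal reference distribution. On 6 df it is about 70%, and lower if classes change differently.

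**A reader might extend the point to every analysis in the section.** The regressions are exploratory ("Multiple linear regression analyses will explore predictive relationships between PL and physical activity levels"), and the ANOVAs compare groups at baseline and test no intervention effect. GEE is only an option for secondary outcomes, and no variance estimator is named, so it cannot be called uncorrected. These are minor and no part of the core claim.

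**Conclusion.** The concern holds in a conditional form. Fitted with the terms listed, the model gives the wrong standard error for the group-by-time effect, and the claim of valid inference is not met. At ICC 0.02 type I error lies between below 0.1% and about 6%, so the usual consequence is a conservative test. It becomes clearly anti-conservative, about 8% to 24%, if class-by-time variance is 0.05 to 0.10. A participant effect alone is not a sufficient repair: at ICC 0.02 type I error is then about 9% to 27% when half or all of the class variance is class-by-time.

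The size rests on the assumed within-student correlation and stability of class effects, neither of which the protocol states. The type I figures use a normal reference, which flatters any analysis that has only eight classes.

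**What to change.** In Data analysis, specify for the intervention models:

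- a participant random intercept, or an unstructured within-participant covariance;
- a class random intercept;
- a class-by-time random effect;
- Kenward-Roger or Satterthwaite degrees of freedom.

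Name a fallback if this does not converge: analyse the eight class-level mean changes with t on about 6 df. If GEE is used for a secondary outcome, cluster on class, with a small-sample-corrected variance and a t reference.

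This costs a few words and a few lines of syntax, with no new data and no change to the design. The downside should be stated openly. With about 6 df, power for a 0.45 SD difference (ICC 0.02, correlation 0.5) is about 70% if class effects are stable and about 46% to 56% if they are not, and confidence intervals may be wider than the class-only model would show.
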